### Primary endpoint and measures

#### Presence or absence of MD in the IMF

Based on the PRO questionnaire (described under *Data Collection* [see Additional file 1]), a positive score of MD in the IMF will be based on a response of “Yes” for open skin within the past seven days (Question 7a) and a non-zero response for “under the breast” as a location of open skin (Question 7b), unless MD is definitively ruled out by a trained and blinded staff assessor.

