### Patient population

This study is designed for patients having large or pendulous breasts resulting in IMF and/or lateral breast ptosis. The oncologist or radiation therapist will use an eligibility checklist to pre-screen for potential participants. Patients receiving nodal RT are eligible assuming the inclusion criteria are met. Enrolment in other studies at the same time is permitted at the discretion of the treating radiation oncologist. Waivers to eligibility criteria are not permitted.

Patient participation will be required for seven weeks after the start of breast RT with PRO questionnaires to be completed weekly, starting the last week of treatment and through to the duration of this seven-week period. Follow-up assessments with staff may be done in the clinic or remotely (e.g. Tele-Health, Zoom, phone, e-mail).

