#### *Statistical methods – *primary* outcome*

The proportion of patients experiencing MD in the IMF in the two arms will be compared using logistic regression to assess the effect of treatment, adjusting for brassiere cup size, skin fold size, BMI, smoking status, and dose fractionation schedule. An unadjusted comparison will also be made using the chi-square test, or Fisher’s exact test, if appropriate. Those participants who do not complete all follow-up but have reported MD are included in the analysis. Those who do not complete all follow-up and do not report MD will be excluded from the primary analysis. A sensitivity analysis including those lost to follow-up will be done using multiple imputations for missing data.

Baseline descriptive variables (e.g., age, smoking status, BMI, as described in the section Baseline Assessment) will be compared descriptively between the two arms of the study and assessed for imbalance. Formal statistical comparisons of baseline characteristics in RCTs are not advised [35].

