### Participant withdrawal

A participant may withdraw from the study for any reason at any time. Patients may also be withdrawn from the study at the discretion of the investigator and/or treatment team, for example, if problems arise with healing of the surgical wound if this interferes with the required skin assessments or causes treatment interruption or delay. Participants withdrawn from the study shall continue to receive appropriate treatment as decided upon with their radiation oncologist. Data collected up to the point of withdrawal will remain in the study.

Patients in the control arm who withdraw from the study post-CT simulation will continue with treatment as planned, with no interruption. Patients in the experimental study arm who withdraw from the study will decide, in discussion with the treating oncologist, whether to continue with CARA or to change to the standard of care breast positioning method. In the latter case, the patient will be required to undergo repeat CT simulation and planning with the standard method. This process typically requires one week and may be done currently with continued treatment with CARA if desired. Otherwise, a treatment interruption may be required.

A participant is considered to have completed the study if they have completed all phases of the study including treatment and the final PRO questionnaire. If a participant fails to complete a follow-up PRO assessment, the site will attempt to contact the participant weekly and counsel the participant on the importance of maintaining the assigned follow-up schedule and ascertain whether the participant wishes to and/or should continue in the study. Should the participant remain unreachable out to eight weeks from the start of RT, they will be considered to have withdrawn from the study.

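### The primary analysis keeps incomplete patients who reported moist desquamation, drops incomplete patients who did not, and never says what counts as complete follow-up

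*Protocol article*

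**What the plan says.** All references are to the protocol article.

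- **Endpoint** (Presence or absence of MD in the IMF). MD is scored from a positive answer "for open skin within the past seven days (Question 7a") plus a location under the breast, unless a trained, blinded assessor definitively rules it out.
- **Schedule** (Patient population). "PRO questionnaires to be completed weekly, starting the last week of treatment and through to the duration of this seven-week period". Table 1 also lists the questionnaire weekly during radiotherapy.
- **Analysis set** (Statistical methods – primary outcome). "Those participants who do not complete all follow-up but have reported MD are included in the analysis". The next sentence reads: "Those who do not complete all follow-up and do not report MD will be excluded from the primary analysis".
- **Missing data** (same section). "A sensitivity analysis including those lost to follow-up will be done using multiple imputations for missing data".
- **Completion** (Participant withdrawal). A participant has completed the study on having "completed all phases of the study including treatment and the final PRO questionnaire". Missed forms lead to weekly contact attempts, and: "Should the participant remain unreachable out to eight weeks from the start of RT, they will be considered to have withdrawn from the study".
- **Staff assessment** (Table 1; Staff skin assessments). Required at baseline and in the last week of treatment (on the last day for five fractions). Afterwards it depends on the patient's preference.

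**The concern.** Two patients can have the same gap in follow-up. The one who reported MD is analysed and the one who did not is removed. This raises the MD proportion in both arms. It also shifts the treatment effect if completeness among MD-free patients differs between arms, which is plausible because patients know their positioning method.

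How many patients are removed turns on an undefined phrase. If complete follow-up means every weekly form, a single lapse removes an MD-free patient. If it means the completion rule under Participant withdrawal, which names only treatment and the last form, a patient can be silent through the weeks after radiotherapy and still count as an observed non-case. The last form looks back seven days and cannot recover the earlier weeks. She was not lost to follow-up, so the planned imputation does not cover her. The Background itself says that failing to monitor out to two weeks after treatment can cause MD to be under-reported.

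At stake are the primary proportions, the analysable number and, under unequal response, the effect estimate.

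**Working it through.** **1. The plan's own sample size.** Inputs from Sample size calculation: 50% vs 30%, two-tailed α = 0.05, 80% power. With pooled variance and no continuity correction,
n = [1.96·√(2·0.40·0.60) + 0.8416·√(0.25 + 0.21)]² / 0.20² = (1.358 + 0.571)² / 0.04 ≈ 93 per arm.
This matches the stated 93. Enrolling 110 and losing 10% leaves 99 per arm, with power 82%. The sample size is not in dispute.

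**2. Literal reading: every form required.** Let c be the completion probability per form (assumed, independent between forms), k the number of forms, q = c^k, and p the true MD rate. Assume every MD case is still reported.
Number analysed = 110·[p + (1 − p)·q]; observed rate = p / [p + (1 − p)·q].

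With c = 0.95 and k = 7, q = 0.698:
- Control: 110·(0.5 + 0.5·0.698) = 93.4; rate 0.5/0.849 = 58.9%.
- CARA: 110·(0.3 + 0.7·0.698) = 86.8; rate 0.3/0.789 = 38.0%.

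The difference is 20.9 points, with power 80%. With c = 0.90, q = 0.478: 81 and 70 patients remain, the rates are 67.6% and 47.3%, and power is 72%. CARA loses more patients because more of them are expected to be MD-free.

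Seven forms is the count for 5 fractions under Patient population, and roughly the count for every schedule under Table 1. If only Patient population applies, the forms number 5, 4, 3 and 2 for 15, 16, 25 and 28 fractions, and q at c = 0.95 is 77%, 81%, 86% and 90%.

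**3. Effect of the outcome-dependent exclusion.** If the same share of MD-free patients is dropped in both arms, that share cancels from the odds ratio. It stays at (0.3/0.7)/(0.5/0.5) = 0.43, and only the proportions move. If the shares differ, the effect moves:

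| MD-free patients dropped, control / CARA | Observed rates | Difference | Odds ratio | Power |
|---|---|---|---|---|
| 10% / 10% | 52.6% / 32.3% | 20.4 points | 0.43 | 85% |
| 5% / 15% | 51.3% / 33.5% | 17.8 points | 0.43·0.95/0.85 = 0.48 | 73% |
| 15% / 5% | 54.1% / 31.1% | 23.0 points | 0.43·0.85/0.95 = 0.38 | 92% |

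**4. Reading through the completion rule.** Let m be the share of true MD cases that go unreported in missing weeks while the last form is returned (assumed). Observed rate = p·(1 − m), with 99 per arm:

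| m, control / CARA | Observed rates | Difference | Power |
|---|---|---|---|
| 0 / 0 | 50% / 30% | 20 points | 82% |
| 5% / 5% | 47.5% / 28.5% | 19 points | 79% |
| 10% / 10% | 45% / 27% | 18 points | 76% |
| 20% / 20% | 40% / 24% | 16 points | 68% |
| 15% / 5% | 42.5% / 28.5% | 14 points | 54% |
| 5% / 15% | 47.5% / 25.5% | 22 points | 90% |

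**5. Missing only week 7.** At five fractions a week, two weeks after radiotherapy falls at week (fractions/5) + 2: 3.0, 5.0, 5.2, 7.0 and 7.6 for 5, 15, 16, 25 and 28 fractions. For the first three the week-7 form lies beyond that point. Yet an MD-free patient who answered every form to week 6 is excluded under both readings. For 25 and 28 fractions the week-7 form lies inside the two weeks, so its absence does matter.

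**The case against.** The strongest reply is that the completion rule describes participant disposition, not the analysis set. The analysis section does not refer to it, and its phrase about all phases may require more than the last form. On that view a patient with missing weeks is excluded rather than scored MD-free. A reader might infer that such patients definitely count as MD-free, or that the two sections contradict each other. The article supports neither: the first holds under one reading only, and study completion and evaluability are different statuses. What stands is that the phrase is open and each reading has a cost.

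A second reply is that handling of intermittent gaps belongs in the full protocol or analysis plan. That would answer a mere omission. Here the article states an exclusion rule and limits the imputation, and both are fixed badly.

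Other points reduce the size:
- Late responders are contacted, paper and assisted completion are offered, staff assess skin in the last treatment week, and imputation brings back those lost to follow-up in a sensitivity analysis.
- With equal completeness in the two arms, the odds ratio from the planned logistic model is not shifted by the exclusion (step 3).
- A reader might infer that exclusion depends strongly on fractionation. That needs the Patient population schedule alone; Table 1's weekly on-treatment forms largely remove the gradient. Fractionation is also a stratification factor and a covariate.
- A reader might infer that the week-7 form carries almost no information. This is wrong for 25 and 28 fractions. For the shorter schedules too, the Background's two-week remark is a minimum for standard schedules, not an end of risk.

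**Conclusion.** The concern holds in this form: the primary analysis set is selected on the outcome, by a rule whose key term is undefined, and neither available reading is sound. The literal reading could leave the CARA arm below the 93 required (about 87 of 110) and report about 59% vs 38% where 50% vs 30% is true. The other reading hides unreported MD: 5% to 10% hidden equally costs 3 to 6 points of power, and unequal hiding of 15% vs 5% moves the difference to 14 or 22 points. Under both readings an MD-free patient on 5, 15 or 16 fractions who misses only week 7 is dropped.

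These sizes rest on assumed missingness, independence between forms, and the planned rates; the article gives no questionnaire completion rate. Clustered missingness would raise the share with all forms complete and soften the literal-reading figures. The existence of outcome-dependent inclusion rests on no assumption. This should be corrected, but it does not invalidate the design.

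**What to change.** In Statistical methods – primary outcome, replace the exclusion sentence with one evaluability rule:

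- **MD-positive**: MD in the IMF reported at any time, including after the window below, subject to the existing blinded rule-out.
- **Observed MD-free**: no MD reported, and questionnaires or blinded staff assessments cover each week of a prespecified, fractionation-specific window. The window runs from the last radiotherapy week to at least two weeks after radiotherapy, capped at the last scheduled form (week 7). The cap is needed because two weeks after 28 fractions is week 7.6. Justify the 5-fraction window separately, since the Background's timing concerns standard schedules.
- **Otherwise missing**: multiply imputed, including patients with intermittent gaps inside the window and not only those lost to follow-up.

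State that the completion definition under Participant withdrawal concerns disposition only. At the existing catch-up contact, ask Questions 7a and 7b for the whole period since the last completed form and record the dates.

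The cost is a wording change, a date line at a contact that already takes place, slightly less accurate recall at catch-up, and some extra imputation work. Enrolment and the visit schedule do not change.

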### Regulatory/ethical considerations

This study has been reviewed by an appropriate REB and will be conducted in accordance with applicable laws and regulations (e.g. Health Canada device regulations) and ICH-GCP guidelines.

The investigator will provide oversight of the study, including conduct and adherence to guidelines and regulations. Written summaries of the status of the study will be provided to the REB annually (or more frequently, as appropriate) and the REB will be notified of any SAEs, protocol violations, or significant safety findings.

Participating sites will be required to credential for this study by submitting treatment planning test cases and completing skin assessment training. A credentialing committee consisting of a least one physicist and one therapist will review submitted data and confirm when the site is approved. Upon study completion, closure of study sites will include collecting all required documents and supplies and a study-site closure visit. Early study-site closure may be initiated at any time, for reasons including failure to comply with protocols, the REB, ICH-GCP guidelines, local health authorities, or inadequate recruitment of participants.

The results of this study may be published or presented at scientific meetings. Investigators agree to submit all manuscripts or abstracts to the sponsor before submission. This allows the sponsor to protect proprietary information and to provide comments. The sponsor will comply with the requirements for publication of study results. In accordance with standard practice, the sponsor will generally support publication of multicenter studies only in their entirety and not as individual site data. In this case, a coordinating investigator will be designated by mutual agreement. Authorship will be determined by mutual agreement and in line with International Committee of Medical Journal Editors authorship requirements.

## Discussion

There is an unmet need for improved supine breast positioning for patients with large or pendulous breasts undergoing RT. MD in the infra-mammary area is common in this patient population and is associated with decreased quality of life. The primary objective of this study is to determine if positioning with the CARA V3.0 device will reduce the incidence of MD in the IMF compared to the current standard of care. After several preliminary and pilot studies, this is the first RCT to measure the effectiveness of CARA to reduce MD. It is expected that the IMF elimination reduce acute toxicity of RT in this patient population. Several dose-volume and dose-area parameters will be measured to fully appreciate the potential of the CARA intervention. A limitation of this study is that it is focused on acute toxicity measurement and longer-term lung and heart toxicities are not currently included. Future investigation of these endpoints is under consideration. A strength of the study is that we will be measuring clinical workflow factors including setup time, reproducibility, radiation therapist experience, and patient experience to understand factors that may influence the integration of CARA into standard breast RT protocols.

## Data Availability

Not applicable.

## Abbreviations

AE: Adverse Event
BMI: Body Mass Index
CARA: Carbon-Fibre Adjustable Reusable Accessory
CBCT: Cone Beam CT
CT: Computed Tomography
CTCAE: Common Terminology Criteria for Adverse Events
CTV: Clinical Target Volume
DSMC: Data Safety Monitoring Committee
Gy: Gray
ICF: Informed Consent Form
ICH-GCP: International Council for Harmonization—Good Clinical Practice
IMF: Infra-Mammary Fold
IMRT: Intensity Modulated RT
kV: Kilovolt
MD: Moist Desquamation
MV: Megavolt
NCI: National Cancer Institute
OAR: Organ At Risk
OTV: Optimization Target Volume
POSI: Prospective Outcomes and Surveillance Initiative
PTV: Planning Target Volume
PRO: Patient-Reported Outcome
RCT: Randomized Controlled Trial
REB: Research Ethics Board
RT: Radiation Therapy
RTOG: Radiation Therapy Oncology Group
SAE: Serious Adverse Event
V20Gy: Volume of an organ receiving a dose of 20 Gy or more
V105%: Volume of an organ receiving 105% or more of the prescribed dose
